### Length of study (study I–IV)

3.2

The study was conducted till 1 year after the enrollment of last patient.

### Participants

3.3

All new patients with clinical suspicion of PMR/GCA will be offered to be included in the study. At least 5 (A–E) components of the PMR diagnostic criteria, including: age ≥50 years, bilateral shoulder or hip pain, morning stiffness lasting >45 minutes, elevated ESR, elevated CRP, disease duration >2 weeks, should be met to suspect PMR.^[3]^ For GCA, the following criteria must be considered: age >50 years, ESR/CRP >50, and also at least 2 symptoms related to vasculitis (scalp tenderness, vision disturbances, headache [new or changed], jaw claudication, tenderness of the temporal arteria) if patients do not simultaneously have PMR. If the patient is suspected for PMR, 1 cranial symptom is enough to suspect GCA. Besides, clinical suspicion of LV-GCA, that is, upper-extremity claudication, upper-extremity blood pressure discrepancies, and abnormal radial pulse, will be registered.

The exclusion criteria (study I–IV) are as follows:1.Patients with dementia or inability to communicate in Danish2.Infections or malignancy when prednisolone is permanently unsuitable3.Contraindication to imaging studies (pregnancy and blood sugar [BS] >8 mmol/L after 6 hours fasting)4.Initiation of steroid treatment before the 18F-FDG PET/CT scan5.Inability to provide informed consent

### Study design

3.4

#### Study I: the association of clinical picture of polymyalgia rheumatica and giant cell arteritis with 18F-FDG PET/CT findings: 1-year, prospective, blinded explorative study

3.4.1

The current study is a 1-year prospective, blinded, and explorative study. This is the first study of its kind, to our knowledge, to evaluate the association between the clinical picture of PMR/GCA and 18F-FDG PET/CT findings in a prospective setting. Previous study revealed the correlation between serological markers of inflammation and FDG accumulation in PMR.^[7,26–28]^ However, the small sample size was a major limitation. On the contrary, some reports failed to show this correlation.^[9,29,30]^

All included patients initially will undergo an 18F-FDG PET/CT scan. The results of the 18F-FDG PET/CT scans will not be made accessible to the treating physician in daily clinical routine, but unexpected findings or findings requiring further diagnostic tests or intervention will be relayed to the chief physicians responsible for inclusion. The results of 18F-FDG PET/CT scan will be blinded for both the clinicians and patients. During the year after the initial 18F-FDG PET/CT scan, the following clinical data will be monitored: cumulated prednisolone doses (using patient diaries), well-being of the patients (including visual analog scale [VAS], patient's assessment of pain, morning stiffness [minute], VAS for physicians’ evaluation), ESR, CRP, fibrinogen, and the eventual number of relapses. Definition of remission and relapse is based on expert opinion considering the following parameters: patient's assessment of pain, morning stiffness, ESR, CRP, clinical examination findings (eg, shoulder pain/limitation, upper extremity blood pressure discrepancies, vascular bruits and aortic regurgitation murmur), and steroid dose which is required to control symptoms.

After 1 year, the 18F-FDG PET/CT results will be unveiled and these parameters will be compared in the succeeding groups of patients: patients with vasculitis in the large vessels (PET-positive); patients without vasculitis in the large vessels (PET-negative); patients with findings compatible with PMR (PET-positive); and patients with vasculitis in the large vessels together with findings compatible with PMR (PET-positive). The classification of 18F-FDG PET/CT results (PET +/−) is based on visual assessment in a descriptive manner, and also quantitative methods. The visual assessment is based on simple visual assessment of FDG uptake patterns in a descriptive manner (PMR) and a 4-point scale of FDG uptake in the vessels (GCA). The visual assessment will be compared with simple semiquantitative analyses, that is, so-called maximum standard uptake value (SUVmax), a simple delineation of the single voxels with the highest tracer uptake. This is a simple procedure available with the generic software indigenous to the scanners and provided by the vendors, for example, in our case, GE Advantage Server 2.0 (GE Healthcare, Milwaukee, WI). It is easily applicable in clinic, but highly variable and prone to both technical and patient related pitfalls. Thus, a third method of quantification will be employed and compared with the visual assessment and SUVmax, that is, global disease burden,^[31]^ which is based on more elaborate, and therefore technically cumbersome, computations involving segmentation, quantification, and summing of all FDG-avid lesions with pathologic activity defined by predetermined threshold. These metabolically active volumes (MAVs) will be summed to yield a global disease score, a metabolic volume product (MVP) of all PET-positive lesions throughout the body. This seems to be a very robust method, but also somewhat cumbersome to implement in daily clinical practice.

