##### Image analysis

3.4.1.1

Images will be reviewed by 2 nuclear medicine specialists at the Department of Nuclear Medicine at Odense University Hospital who are blinded to clinical and laboratory data. FDG uptake patterns will be recorded in a descriptive manner with regard to nonarterial uptake and recorded in 6 arterial compartments for each individual patient including thoracic and abdominal aorta, carotid, subclavian, femoral, and iliac arteries. A visual 4-point scale, as described by earlier studies,^[7,27–29]^ will be used for every arterial segment as follows:0: No uptake1: Slight uptake but not negligible, lower than liver uptake2: Intermediate uptake, similar to liver uptake3: High-grade intense uptake, higher than liver uptake

A score of ≥2 and <2 will be considered PET-positive and PET-negative, respectively. SUVs will be measured for quantitative analysis for each arterial segment and calculated as follows: 

Global disease burden will be expressed as follows:

cMVP = ∑ (MAV∗cSUVmean), where

cMVP = partial volume corrected metabolic volume product,

MAV = metabolic active volumes, and

cSUVmean = partial volume corrected mean standard uptake value

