### Outcomes

3.8

The primary outcome measure are as follows:1.To evaluate the cumulated prednisolone doses, VAS, patients’ assessment of pain, morning stiffness, VAS for physician evaluation, biochemistry results, that is, ESR, CRP, and fibrinogen, and the eventual number of relapses at baseline and during the first year after treatment initiation (weeks 12, 24, 36, and 48) in patients with PET-positive and PET-negative as described above.

The secondary outcome measures are as follows:1.To elucidate the degree of agreement between PET positivity (vasculitis in the large vessels, and also findings compatible with PMR) and TAB positivity.2.To elucidate the degree of agreement between PET negativity (no signs of vasculitis in the large vessels) and TAB negativity.3.To reveal the prevalence of malignancies in the patients detected by the aim of 18F-FDG PET/CT scan and subsequently compare to the prevalence of malignancies detected by the aim of CXR plus abdominal US.4.To reveal the prevalence of malignancies in the patients detected by the aim of CXR plus abdominal US and subsequently compare to the prevalence of malignancies detected by the aim of 18F-FDG PET/CT scan.5.To evaluate BMI, T score, Z score, LBM, FM, BMD, BMC, FFM, FFMI, and FMI at baseline and after 1 year of treatment initiation.6.To evaluate aortic PWV, upper limb PWV, and aortic augmentation index of included patients at baseline and during treatment (weeks 12, 24, 36, and 48).

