## Discussion

4

The proposed study will explore the potential role of 18F-FDG PET/CT scan in the early diagnosis and management of PMR/GCA before initiation of steroid treatment, and also the association between 18F-FDG PET/CT findings and the clinical picture of the patients. Though 18F-FDG PET/CT is not yet capable of evaluating temporal artery due to inadequate resolution, the extracranial involvement of large vessels, mainly thoracic aorta, carotid, and subclavian, can be delineated.^[53]^ Patients with positive 18F-FDG PET/CT findings will be classified as having GCA and not isolated PMR, which is of great importance in the clinic due to different steroid treatment regimes. Besides, GCA patients with aortic involvement are at increased risk of aneurysm formation, who seek close monitoring.^[54]^ It is our hope that our results elucidate the 3 main areas of concern regarding the management of PMR/GCA including: malignancy, osteoporosis/changes in body composition, the vasculitis process, and the interaction between them, and ultimately elucidate factors predictive of the disease outcome.

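### The PET-positive and PET-negative labels overlap: a patient with PMR-type uptake but no large-vessel vasculitis carries both, and the protocol does not say on which side of the primary comparison that patient belongs

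*Protocol article*

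**What the plan says.** The primary objective (2.1) relates PET positivity or negativity to the clinical picture. The labels are set or used in these places.

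- **Study I (3.4.1)** lists four groups. The first is large-vessel vasculitis, labelled positive. The next two are "patients without vasculitis in the large vessels (PET-negative); patients with findings compatible with PMR (PET-positive"). The last is "patients with vasculitis in the large vessels together with findings compatible with PMR (PET-positive"). The same section bases the classification on a descriptive read for PMR and a 4-point vessel scale for GCA, alongside quantitative methods.
- **Image analysis (3.4.1.1)** scores each arterial segment from 0 to 3 and states: "A score of ≥2 and <2 will be considered PET-positive and PET-negative, respectively". For the rest of the body, "FDG uptake patterns will be recorded in a descriptive manner with regard to nonarterial uptake". No cut-off is given there for non-arterial uptake.
- **Outcomes (3.8)** sets the primary outcome "in patients with PET-positive and PET-negative as described above". For agreement with temporal artery biopsy (TAB), one outcome uses "PET positivity (vasculitis in the large vessels, and also findings compatible with PMR) and TAB positivity" and the next uses "PET negativity (no signs of vasculitis in the large vessels) and TAB negativity".
- **Statistical analysis (3.12)** compares PET-positive with PET-negative patients by the Mann–Whitney U test or Student t test.
- **Dissemination (3.18)** gives the first planned paper a title that contrasts patients with and without vasculitis on PET.

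**The concern.** PET status is the exposure in the primary objective. A two-sample comparison needs each patient in exactly one group. As the Study I list is worded, the positive label can be earned by either of two findings, but the negative label is earned by lacking only one of them. Patients with the other finding alone get both labels.

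If PMR-only patients join the positive arm, the comparison is any PMR or vasculitis uptake against none. If they join the negative arm, it is vasculitis against no vasculitis. These are different clinical questions. While the rule stays open, it could be settled after the outcomes are known. The Sample size section (3.9) also claims sufficient precision for a between-group difference in cumulated prednisolone dose, and that claim cannot be judged until the groups are fixed.

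**Working it through.** **Step 1. Cross-tabulate the definitions.** Let V+ mean large-vessel vasculitis on PET and P+ mean PMR-type non-arterial uptake.

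| Patient | Study I list (3.4.1) | Arterial cut-off (3.4.1.1) | TAB agreement outcomes (3.8) |
|---|---|---|---|
| V+P− | positive | positive | positive if either finding suffices; neither label if both are required |
| V+P+ | positive | positive | positive |
| V−P− | negative | negative | negative |
| V−P+ | **positive and negative** | negative | negative, and also positive if either finding suffices |

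A V+P+ patient fits three of the four listed groups, but all three are labelled positive, so no conflict arises. Only V−P+ is contradictory in the Study I list. In the TAB outcomes, positive and negative are not complements whether the positive definition requires either finding or both.

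**Step 2. Show what the choice does.** The protocol states no group split, effect size or standard deviation for the primary comparison, so there is no figure to reproduce. Only N = 80 comes from the document (3.9). The split is an assumption: 12 V+, 50 V−P+, 18 V−P−.

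- Vasculitis rule: 12 v (50 + 18) = 12 v 68.
- Any-uptake rule: (12 + 50) v 18 = 62 v 18.
- Labels taken literally: 62 + 68 = 130 memberships for 80 patients, so 50 are counted twice.

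**Step 3. Precision.** The 95% CI half-width for a mean difference, in SD units, is t(0.975, 78) × √(1/n1 + 1/n2), with t = 1.99.

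- 12 v 68: 1.99 × √(0.0833 + 0.0147) = 0.62 SD.
- 62 v 18: 1.99 × √(0.0161 + 0.0556) = 0.53 SD.

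**Step 4. Meaning of the contrast.** Suppose, for illustration, that only vasculitis shifts the outcome, by D. The vasculitis rule then has expected difference D. The any-uptake rule has (number V+) / (number V+ plus number V−P+) × D = 12/62 × D = 0.19 D.

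**Step 5. Range.** Nine assumed splits were tried, with V+ from 10% to 30% and V−P+ from 30% to 80%.

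- Literal memberships run from 104 to 144, so 24 to 64 of the 80 patients are counted twice.
- The half-width runs from 0.49 to 0.74 SD under the vasculitis rule and from 0.45 to 0.74 SD under the any-uptake rule.
- The factor in Step 4 runs from 8/72 = 0.11 to 24/48 = 0.50.

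In the Step 2 split, precision changes modestly between the rules, while what is being estimated changes a great deal.

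**The case against.** The best defence is that the labels apply to each read separately. Study I names a descriptive read for PMR and a vessel scale for GCA. On that view a V−P+ patient is vessel-negative and PMR-positive, which is no contradiction. The planned paper title then points to vasculitis yes or no as the contrast, and the study is explorative in any case. This reading is reasonable and would make the analysis runnable. It does not settle the matter, because the primary outcome and the tests use the two labels without saying which read they refer to. The alternative, that negative tacitly means neither finding, is also runnable and moves the same patients to the other arm.

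Four stronger inferences are tempting, and the document does not support them.

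- **That the arterial cut-off is a rival patient-level definition.** It follows a scale applied to each arterial segment and can be read as the threshold for the vessel read alone.
- **That the Discussion assigns every PET-positive patient to GCA.** It says "Patients with positive 18F-FDG PET/CT findings will be classified as having GCA and not isolated PMR", but the neighbouring sentences concern large-vessel and aortic involvement, so vascular findings are the natural meaning.
- **That no table against TAB can be built.** Vasculitis by TAB can be tabulated, and only descriptive statistics and proportions of agreement are planned. What is unclear is the role of PMR findings in the first agreement outcome.
- **That reads could be fitted to outcomes.** The image readers are blinded to clinical and laboratory data. Only the grouping rule is open.

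**Conclusion.** The concern stands as an internal contradiction in the primary exposure. It is not a detail left to an analysis plan, because the stated definitions conflict and the primary outcome refers back to them. It is confined to patients with PMR-type uptake and no vasculitis, plus the non-complementary definitions in the TAB outcomes.

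A reader might conclude that the primary comparison is impossible. That goes too far: it can be run once a rule is chosen, but the protocol does not choose one.

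The number of patients affected cannot be taken from the document. The 12/50/18 split is assumed, and nothing in the protocol shows that PMR-only uptake will be the largest group. The factor of 0.19 further assumes that PMR uptake has no effect on outcome, which Study I is meant to explore. These figures show that the two readings can give very different contrasts; they do not measure this trial. The contradiction itself rests on the wording alone. It should be corrected before the PET results are unveiled, since the primary comparison depends on it.

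**What to change.** Before unveiling:

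1. **Define two binary reads.** V+ is any arterial segment scored 2 or higher. P+ is PMR-type non-arterial uptake, with a stated reading rule, because that uptake is at present only described.
2. **Replace the list in 3.4.1** by four exclusive cells: V+P+, V+P−, V−P+ and V−P−.
3. **State which cells form PET-positive and PET-negative** for the primary comparison. V+ against V− fits the arterial cut-off in 3.4.1.1 and the planned paper title in 3.18, with P reported as a second factor. Another rule would also remove the contradiction, provided it is fixed in advance.
4. **In 3.8, make the positive and negative definitions complementary** for TAB agreement. Use one table of vasculitis by TAB, and report any comparison of PMR uptake with TAB separately so that this part of the outcome is kept.
5. **Align the wording of 3.4.1.1 and 3.12** with the chosen rule.

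The cost is wording in these sections and agreement on a P+ rule. No new scans are needed. Choosing V+ against V− could leave a small positive arm; in the illustration it has 12 patients and a half-width of 0.62 SD, against 0.53 SD under the any-uptake rule.

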Positron emission tomography/computed tomography (PET/CT) is a whole-body scan combining molecular and structural imaging in a single examination. The principle is tomographic detection of radiation from intravenously administered radio-labeled tracers targeting disease processes on a cellular or molecular level. Due to its high sensitivity and an inborn ability for quantification, PET can detect diseases at their very early stage and grade their degree of activity.^[17,18]^ The most versatile and widely used tracer, 18F-fluorodeoxyglucose (FDG), is a glucose analog depicting local hypermetabolism (ie, inflammation or cancer). In the clinic, it has mainly been used to detect focal hypermetabolism due to cancer, and the impact in the oncologic domain has been huge as PET/CT appears to cause a change in management in as many as every third patient.^[19]^ However, FDG is nonspecific for cancer as inflammatory lesions also show increased FDG uptake. This was until recently seen as a downside resulting in “false-positive” findings in oncology, but is now considered a great asset, since this allows for detection and characterization of inflammatory processes in many settings. 18F-FDG PET/CT is being investigated clinically in a multitude of inflammatory disorders. High sensitivity, high target-to-background contrast, accurate anatomical localization of sites of inflammation, and an absolute quantification potential may all lead to early assessment of disease processes and their extent.^[20]^

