With regard to vasculitis, recent literature emphasizes the ability of 18F-FDG PET/CT to assess inflammation in the vessel walls, whereas FDG uptake patterns in PMR are not yet firmly established. It may locate disease at an earlier stage than conventional imaging and assess response to therapy. Response assessment is based on changes in glucose metabolism from baseline to post-treatment follow-up, and the rates of change are different in responders and nonresponders.^[21]^ Besides locating focal disease, 18F-FDG PET/CT may also assess disease activity more globally, which may be especially interesting in systemic inflammatory diseases. Thus, this research protocol will also incorporate assessment of global disease assessment (ie, “global disease burden”), a novel approach to quantifying disease. By way of novel software-based quantitative methods, the radioactivity throughout the body can be quantified, summed, and presented as 1 single number, the systemic inflammatory activity or “global disease burden.” The method is new and not yet firmly established, but it holds significant promise, especially for response assessment in systemic inflammatory diseases.^[22,23]^

Therefore, we plan to conduct a prospective study to explore the role of 18F-FDG PET/CT scan in the management of PMR/GCA. In addition, 3 significant areas of concern in the management of PMR/GCA including: osteoporosis due to steroid treatment or disease characteristics itself, malignancy, and vasculitis/vascular stiffness will be investigated during the project. This research protocol consists of four separate studies designed to achieve below mentioned objectives that are discussed individually later in the text (Fig. 1).

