This study is a blinded prospective investigation. At diagnosis all patients undergo a CXR and abdominal US, as recommended by the Danish Rheumatology Association. The 18F-FDG PET/CT scan in every included patient (as described in study I) will be assessed with regards to malignancies before results are blinded to the clinicians for 1 year. This assessment will be blinded to other clinical and imaging results and findings on 18F-FDG PET/CT scan will be compared with CXR/abdominal US results to establish the relative diagnostic accuracy of these 2 strategies for malignant and infectious diseases in PMR/GCA patients. In case of detecting or developing any kinds of malignant disease during the study, the patients will be referred to the relevant department for further work-up and treatment. This will not be a reason for exclusion, but depends on individual assessment of the patient. 18F-FDG PET/CT scan may also be repeated for individual patient if necessary.

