This study is a 1-year prospective investigation which assesses 2 different areas of concern in PMR/GCA patients, namely BMD plus body composition and vasculitis/vascular stiffness of large vessels (aorta). The following procedures will be performed in all included patients:1.PWV measurement of aorta at baseline and then every 3 months to assess large vessels involvement (aorta). The results of PWV assessment, which will be automatically calculated from measurements of pulse transit time and distance between the 2 sites, will be compared with vasculitis found in the 18F-FDG PET/CT (study I). The results of PWV of aorta will also be assessed regarding the actual cumulated prednisolone dose to find out the effects of steroid treatment on the arterial stiffness.2.Whole-body DXA scan at baseline and after 1 year from the initiation of study to evaluate BMD and body compositions. The degree of the difference in the T score and body composition (including lean body mass, fat mass, bone mineral content, and BMD) will be compared with the cumulated prednisolone dose and the total global disease burden of the 18F-FDG PET/CT scan at baseline (study I).

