### Statistical analysis

3.12

It is anticipated that 80 participants are likely to be included during a period of 1 year. The results will be considered as significant if *P* value <0.05. Statistical analysis has been discussed below with respect to each individual study.

In study I, data will be descriptive (mean ± standard deviation). Comparisons of the data, between the PET-positive and PET-negative patients, will be made with the Mann–Whitney *U* test or Student *t* test, depending on whether or not the distribution is normal. When comparing 2 binary variables, the chi-square test will be performed. Correlation analysis will be performed with Pearson correlation test.

Study II consists of descriptive statistics and proportions of agreement.

Study III consists of descriptive statistics. Comparisons between groups will be made with McNemar test. The sample size of 80 patients is sufficient to indicate a difference of 15% in detection rate of malignancies with 18F-FDG PET-CT scan as opposed to CXR plus abdominal UL (with a significance level of 5% (1-sided), power of 80%, and assuming discordant proportions of 15% and 0%).^[52]^

Study IV consists of descriptive statistics. Univariate comparisons between groups will be made with the Mann–Whitney *U* test or Student *t* test, depending on whether or not the distribution is normal. When comparing 2 binary variables, the chi-square test will be performed. Analysis of repeated measurements over time will be done by means of mixed linear models, using standard errors that allow for intragroup correlation, relaxing the usual requirement that the observations be independent. Comparison of the above mentioned baseline data, matched by age and sex, will be made, to the extent that these data are available.

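### Global disease burden (cMVP) is defined as the sum of all FDG-avid lesions in the body, so as written it counts tumour and infection uptake as PMR/GCA inflammatory activity

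*Protocol article*

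**What the plan says.** Section 3.4.1 (Study I) introduces a third way of quantifying the scans, after visual assessment and SUVmax. It consists of "segmentation, quantification, and summing of all FDG-avid lesions with pathologic activity defined by predetermined threshold", and the volumes are added to give "a metabolic volume product (MVP) of all PET-positive lesions throughout the body". Section 3.4.1.1 writes this as cMVP = Σ(MAV × cSUVmean), with no restriction on the site or cause of a lesion.

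The Introduction gives the sum its meaning: "the radioactivity throughout the body can be quantified, summed, and presented as 1 single number, the systemic inflammatory activity". The same Introduction also states that "FDG is nonspecific for cancer as inflammatory lesions also show increased FDG uptake".

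Section 3.3 excludes patients under the heading "Infections or malignancy when prednisolone is permanently unsuitable", so other patients with infection or malignancy remain eligible. Section 3.4.3 (Study III) reads the same baseline scans for malignant and infectious disease. On a malignancy found or developing during the study it says: "This will not be a reason for exclusion, but depends on individual assessment of the patient".

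Section 3.4.4 (Study IV) then compares one-year changes in T score and body composition with the baseline global disease burden from Study I.

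**The concern.** A score read as systemic inflammatory activity should contain only uptake that the disease could have produced. The stated rule has one filter, an activity threshold. A tumour or a pneumonia passes it as readily as an inflamed aorta or shoulder.

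Two uses are exposed:

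- **Study I.** cMVP is compared with the visual assessment and SUVmax. For arteries these are recorded by segment, so a tumour outside the vessels would raise cMVP and leave the arterial readings unchanged. The methods would then disagree for a reason unrelated to PMR/GCA.
- **Study IV.** Baseline burden is set against changes in bone and body composition. Uptake unrelated to PMR/GCA adds noise to the explanatory variable and tends to weaken any true relation.

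Section 3.12 names Pearson correlation for Study I. That method is more sensitive to a few large values than a rank correlation.

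**Working it through.** **1. Does the text remove such lesions anywhere?** Four statements, side by side:

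| Question | Where | What it fixes |
|---|---|---|
| What is summed? | 3.4.1, 3.4.1.1 | All FDG-avid lesions above a threshold, whole body |
| What does the sum mean? | Introduction | Systemic inflammatory activity |
| Does FDG separate cancer from inflammation? | Introduction | No |
| Are patients with malignancy or infection out? | 3.3, 3.4.3 | Only where prednisolone is permanently unsuitable; a malignancy found later is judged individually |

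No statement in the article removes malignant or infectious lesions from the sum, or the patients who have them from the burden analyses. The definitional point follows from this and needs no arithmetic.

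**2. How many of the 80 scans might be affected?** The documents give no expected share.

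- Section 3.12 plans Study III with malignancy seen on PET/CT only in 15% and on the conventional work-up only in 0%. That would be 0.15 × 80 = 12 patients, but it is a power assumption, not a forecast.
- The UK cohort cited in 3.4.3 points lower. Controls: 19.5% / 7.8 years = 2.5% a year, or 1.25% in six months. Times the early hazard ratio of 1.69, this is about 2.1%, and 0.021 × 80 = 1.7 patients. This is crude: it counts diagnosed cancers, not cancers visible on a baseline scan, and it leaves out infection.
- With a share p, the chance of at least one affected scan is 1 − (1 − p)^80: 55% at 1%, 80% at 2%, 98% at 5%.

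**3. What could that do to a correlation?** This is an illustration only. Assumptions: n = 80; inflammatory burden exp(0.8z) with z standard normal; an outcome correlated 0.4 with z; in a share p of patients a tumour adds a fixed multiple of the median burden, unrelated to the outcome; burden analysed untransformed; two-sided 5% test.

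| Share, tumour size | Mean Pearson r | Share significant | Mean Spearman r |
|---|---|---|---|
| none | 0.35 | 90% | 0.38 |
| 3%, 1× median | 0.35 | 90% | 0.37 |
| 3%, 5× | 0.29 | 75% | 0.36 |
| 6%, 5× | 0.25 | 62% | 0.34 |
| 15%, 2× | 0.30 | 77–78% | 0.31 |
| 15%, 5× | 0.20 | 43–46% | 0.29 |

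The first row is 0.35 and not 0.40 because the raw burden is skewed. If tumour size also varies (log-normal, log-SD 0.8, assumed), the Pearson loss is larger: about 0.24 (58%) at 15%/2× and 0.13 (24%) at 15%/5×.

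**The case against.** **cMVP is not an outcome.** This stands. Section 3.8 lists one primary and six secondary items, and global disease burden is in none of them. The Introduction calls the method new and not firmly established, and 3.9 calls the study exploratory. A reader might infer that an endpoint of the trial is compromised; the documents do not support that.

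**The intended meaning may be narrower.** Elsewhere in 3.4.1 and 3.4.1.1, PET-positive refers to large-vessel vasculitis, findings compatible with PMR, or an arterial score of 2 or more. A sum over PET-positive lesions could therefore mean PMR/GCA lesions only. That reading is possible, but it does not displace the operative clause, which takes all FDG-avid lesions by threshold. The restriction to pathologic activity does deal with physiological uptake; it does not deal with tumour or infection, which are pathologic.

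**The full protocol may hold a lesion-selection rule.** It may. But the article is not silent on the matter: it states a rule, and the rule as stated gives the wrong quantity.

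**Contamination is already limited.** In part. There is a primary investigation before enrolment, some malignancies and infections are excluded, and continuation after a cancer finding is decided individually. These steps reduce the number of affected scans but do not ensure there are none.

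**The size is speculative.** This largely stands. A reader might take 15% of 80 as an expected 12 scans with tumour uptake; section 3.12 gives it only as the assumption behind a detectable difference. A reader might also infer that affected patients must be extreme outliers, or that tumours would create a false link between burden and loss of lean or fat mass. The documents give no tumour or inflammatory volumes and no figure for such a link, so neither can be asserted.

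**Conclusion.** The point holds as a fault of definition. Followed as written, cMVP counts tumour and infection uptake as systemic inflammatory activity, although the article itself says the tracer cannot tell them apart and does not automatically exclude the patients concerned. It affects the comparison of quantification methods in Study I and one explanatory variable in Study IV. It does not touch a listed outcome or the sample-size statements.

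The size cannot be derived from the documents. On the assumptions shown, the effect on a Pearson correlation runs from negligible (3% of scans, tumours equal to the median burden) to substantial (0.35 to 0.20 with 15% of scans and tumours five times the median), and further if tumour size varies. Rank correlation is less affected, falling from 0.38 to between 0.37 and 0.29. It is worth correcting because the correction is cheap, not because a large distortion has been shown.

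**What to change.** In 3.4.1 and 3.4.1.1, define cMVP as the sum over FDG-avid lesions that the nuclear medicine readers have not classified as malignant, infectious or otherwise unrelated to PMR/GCA. Take the classification from the reading for malignant and infectious disease that Study III already requires. It is made blinded to other clinical and imaging results, so the labels can be fixed before burden is related to any clinical variable. Use this cMVP in Studies I and IV, and report the all-lesion sum as a sensitivity analysis.

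The cost is one sentence of definition and a label per lesion at segmentation. No new scan, visit or patient is needed. The small downside is some reader judgement in attributing lesions; the all-lesion sensitivity analysis shows how much depends on it.
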